#### Missing data

‘Missingness’ is considered to be missing at random and mixed methods repeated measures (MMRM) and multiple imputation techniques will be used for handling missing data. In particular, for continuous outcomes at multiple time points MMRM will be used.

#### Sample size justification

Based on a study of patients with NICM (prior to availability of CMR) a myocardial biopsy adds a specific diagnosis to standard approaches in 15% of patients with NICM increasing the rate from 35% to 50% [7]. For the sample size determination, the estimated occurrence of a definitive diagnosis with CMR is 50% and echo (with selective use of CMR) is 35%. For the primary analysis comparing routine CMR versus selective CMR with a sample size of 252 per group is required to detect a difference in the event rate of definitive diagnosis of cardiomyopathy of 35% (selective CMR) versus 50% (routine CMR), based on the Z-test with a pooled variance estimate, and after adjustment for 10% patient loss or withdrawal, we will be able to detect a difference in the event rate of definitive diagnosis of cardiomyopathy of 35% (selective CMR) versus 50% (routine CMR), a level of significance of 0.05, power of 90% and an adjustment for 10% patient loss or withdrawal.

### Study management

The IMAGE-HF trial is managed by an Executive Committee consisting of clinicians specialized in diagnostic imaging and/or heart failure and experts in biostatistics, physics and radiochemistry, as well as a larger Steering Committee consisting of members of the Executive Committee and representatives of all the initial study centers. In addition there is an events adjudication committee which will independently review and adjudicate each clinical event blinded to treatment randomization. Since all the imaging approaches are part of standard clinical practice, no interim analysis is planned but there will be an independent Data Safety Monitoring Board (DSMB) which will review the safety data on a periodic basis; the frequency of the meetings and the charter governing the DSMB will be finalized at the first meeting of the DSMB.

## Discussion

Multicenter randomized controlled trials are needed to evaluate the emerging role of advanced cardiac imaging in heart failure. CMR is increasingly advocated as a useful tool to evaluate the diagnosis and prognosis of non-ischemic HF patients, but to date there is little evidence to show that outcomes have improved. In IMAGE-HF 1-B, Canadian and Finnish tertiary care sites with access to CMR will randomize non-ischemic HF patients to routine CMR in order to determine whether there are any gains over current imaging strategies employing selective CMR utilization. All patients in this trial will undergo a comprehensive baseline echocardiogram as recommended in HF guidelines.

The design of this trial has several appealing aspects:

First, we will evaluate the role of CMR in HF in a real world setting. Given differences in MRI access, local imaging expertise and in the interpretation of guidelines, the use of CMR in non-ischemic HF can vary greatly in a tertiary care setting. In the proposed randomized trial, we will study whether routine CMR offer any diagnostic gains over a more judicious approach. Such a strategy will thus emulate centers with open CMR access versus those without and determine what if any impact this has on actual patient management. All imaging studies, echo and CMR, will be part of the overall clinical care received by the patient. We also feel that the multicenter design with varying level of CMR expertise and the inclusion of new or worsening HF patients will provide a real world experience.

Second, we will be able to determine whether CMR diagnoses in non-ischemic HF differ from echo diagnoses. The influence that the echo and CMR diagnoses have on the treating physician’s HF diagnosis will be examined. Also, the reproducibility of the imaging diagnoses will be determined in 10% of CMRs and echos as part of our quality assurance analysis.

Third, the potential for routine CMR to guide HF pharmacotherapy and to initiate disease specific treatment will be evaluated. CMR should uncover HF etiologies, such as myocardial infiltration, that was not previously detected by echo and other baseline testing. The treating physician could then prescribe treatment that is more tailored to the underlying pathology.

Fourth, we will determine the impact of routine CMR on the outcomes of non-ischemic HF patients. Most advanced cardiac imaging studies evaluate the diagnostic accuracy of a given modality with no assessment on patient outcome. In a secondary analysis, we will evaluate clinical outcomes including: a composite clinical end-point (death, CV death and HF admission) and two quality of life surveys: MLHFQ and EQ5D. We will also ascertain the feasibility of implementing a routine CMR approach in terms of safety and cost.

### Limitations

Given that CMR provides insight into myocardial characterization, we expect that the etiology of heart failure will be better characterized in those HF patients undergoing routine CMR. However, in some instances additional investigations such as myocardial biopsy and invasive hemodynamics may be required to confirm CMR findings. Therefore, the final diagnosis of heart failure etiology may ultimately be determined by CMR driven ancillary testing. We will assess the impact of downstream resource utilization on diagnosis and outcome in the multivariable analysis as well as calculate the additional cost burden.

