### Primary outcome measure - frequency of definitive diagnoses

Following the completion of all baseline testing (including echo ± CMR), the treating physician will assign a diagnosis on a standardized template using all available information. The HF categories include: idiopathic dilated cardiomyopathy, infiltrative cardiomyopathy, inflammatory cardiomyopathy, hypertrophic cardiomyopathy, heart failure with preserved ejection fraction (HFPEF), ischemic cardiomyopathy, mixed etiology and other (for example, pericardial disease, adult congenital heart disease, arrhythmogenic right ventricular cardiomyopathy). The diagnosis of non-ischemic cardiomyopathies will be based upon the 2008 Canadian Cardiovascular Society Consensus conference guidelines [37].

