### Secondary outcome measures

(i) Treatment effects: at three months and one year, the treating physician will be asked to reassess the HF etiology. The presence of each HF medication class will be re-assessed in addition to the overall number of cardiac medications. The presence of advanced HF therapies will additionally be recorded at each follow-up visit including: implantable device, electrophysiologic study/ablation, cardiac surgery/transplantation, and disease specific therapies (for example, phlebotomy for hemochromatosis; steroids for sarcoidosis).

(ii) Clinical endpoints: Composite Clinical Endpoints (CCE that is, death, cardiovascular (CV) death, HF admission), left ventricular function, QoL, referral to HF clinic, costs and safety will be assessed at three months, then annually for a minimum of one year and a maximum of four years.

Resource utilization and costs: regression methods will be used to assess the incremental costs associated with the routine use of CMR.

(iii) Echo/CMR variability: anonymized copies of CMR and echo studies will be sent to a core lab for interpretation in approximately 10% of cases in order to assess reproducibility and quality assurance of the results. Appendix A.

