#### Primary analysis

For the primary analysis, the definitive diagnosis of cardiomyopathy between routine CMR versus echo with selective CMR, diagnosis will be compared using chi-square techniques. Potential confounding variables of the relationship between the imaging strategies and the primary endpoint will be assessed. In particular, propensity scores based on patient factors (for example, in/outpatient, NYHA class, HF duration, diabetes, atrial fibrillation) and site factors (for example, time-to-imaging, time-to-therapy) will be used in the analysis if necessary to adjust for potential differences. A logistic regression model will be used to assess the occurrence of the endpoints between the imaging strategies (model will include a group indicator variable) adjusting for any pertinent baseline differences identified.

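### Downstream resource use arises after randomisation; as a fixed covariate for diagnosis and clinical outcome it can give biased estimates and absorb part of the strategy effect

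*Protocol article*

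**What the plan says.** All references are to the protocol article.

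- **Limitations.** Biopsy or invasive hemodynamics may be needed to confirm CMR findings, so "the final diagnosis of heart failure etiology may ultimately be determined by CMR driven ancillary testing". The response is: "We will assess the impact of downstream resource utilization on diagnosis and outcome in the multivariable analysis". The additional cost is also to be calculated.
- **Primary outcome measure.** "Following the completion of all baseline testing (including echo ± CMR), the treating physician will assign a diagnosis". The physician draws on whatever information is available at that point; no rule excludes a test prompted by CMR.
- **Secondary outcome measures.** For etiology, "at three months and one year, the treating physician will be asked to reassess the HF etiology". The clinical composite is given as "CCE that is, death, cardiovascular (CV) death, HF admission", assessed at three months and then "annually for a minimum of one year and a maximum of four years".
- **Primary analysis and Secondary outcomes (statistical analysis).** The diagnosis is compared by chi-square, with a logistic model that holds a group indicator, "adjusting for any pertinent baseline differences identified". Binary secondary outcomes, the CCE among them, are handled the same way. No landmark, time-to-event or time-dependent method is named.

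**The concern.** The sentence in Limitations makes downstream use the explanatory variable, and diagnosis and outcome the dependent variables. The multivariable analysis it refers to can only be matched, within the article, to the logistic models under Statistical analysis. Those were written for baseline differences, and downstream use is not a baseline variable. Three problems follow if it is entered as a fixed term.

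1. **Outcome.** A patient must be alive to be tested. Use counted over follow-up therefore marks out survivors, while sicker patients may be tested more. Neither association is an effect of testing. HF admission may also count both as resource use and as a CCE event, which would put one event on both sides of the model.
2. **Strategy effect.** Limitations describes a chain from CMR to ancillary test to diagnosis. A model with both arm and downstream use conditions on a step in that chain.
3. **Diagnosis.** If the dependent variable is the diagnosis assigned after baseline testing, later tests may have been ordered because of it, and the coefficient would run backwards.

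At stake is whether the trial can say anything sound about testing prompted by CMR, which is the limitation the article itself raises.

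**Working it through.** **The plan's own figures.** The article gives none for this analysis. Its sample size does reproduce: 35% v 50%, two-sided 0.05, 90% power and pooled variance give 227 per group, and 227/0.90 = 252.2, rounded up to 253, against 252 stated. That has no bearing here. All testing and death rates below are assumptions.

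**1. Immortal time, one-year death.** The test truly has no effect (risk ratio 1). A fraction q of patients is scheduled for a test at a time uniform on (0, w) years, and the death hazard is a constant h per year.

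- Probability of being alive at the scheduled test: E = (1 − exp(−hw))/(hw)
- Death by one year, tested: 1 − exp(−h)/E
- Death by one year, never tested: [1 − exp(−h) − q(E − exp(−h))]/(1 − qE)

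With h = 0.15 and q = 0.30, exp(−h) = 0.8607 and overall one-year death is 0.1393.

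| | w = 1 year | w = 3 months |
|---|---|---|
| E | 0.9286 | 0.9815 |
| Tested | 1 − 0.8607/0.9286 = 7.3% | 1 − 0.8607/0.9815 = 12.3% |
| Never tested | (0.1393 − 0.0204)/0.7214 = 16.5% | (0.1393 − 0.0362)/0.7056 = 14.6% |
| Risk ratio | 0.44 | 0.84 |
| Range, h 0.05 to 0.20 and q 0.20 to 0.30 | 0.42 to 0.48 | about 0.83 to 0.86 |

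**2. The same bias over four years.** This was simulated with exponential times to death and to test, 20% tested in the absence of death, four-year mortality of 10% to 40%, and no true effect. The odds ratio for death with ever-tested as a fixed covariate is:

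- 0.95 to 0.96 if tests fall within three months
- 0.82 to 0.85 if within twelve months
- 0.42 to 0.45 if spread over four years

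The size depends almost entirely on when the tests occur. Confounding by indication is not in these figures and could push the other way.

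**3. Conditioning on a step in the chain.** Assume 30% are tested under routine CMR and 5% under selective CMR, with a specific diagnosis in 85% of those tested and 35% of the rest.

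- Routine: 0.30 × 0.85 + 0.70 × 0.35 = 50.0%
- Selective: 0.05 × 0.85 + 0.95 × 0.35 = 37.5%

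The strategy effect is 12.5 points. Within tested patients, and within untested patients, the arms do not differ, so the arm effect is 0 once testing is in the model. This is the extreme case, where the whole gain runs through testing.

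**4. Reverse direction, only if the baseline diagnosis is the dependent variable.** Tests follow the diagnosis and do not influence it. The odds ratio is [a/(1 − a)]/[b/(1 − b)], where a and b are the proportions later tested with and without a specific label.

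- a = 20%, b = 5%: 0.2500/0.0526 = 4.75
- a = 40%, b = 5%: 0.6667/0.0526 = 12.7
- a = 20%, b = 10%: 0.2500/0.1111 = 2.25
- a = b: 1.0

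Steps 3 and 4 are alternatives. In step 3 the test determines the diagnosis; in step 4 it has no influence on it. They cannot both describe the same diagnosis variable.

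**The case against.** A reader might infer that the plan regresses a diagnosis on tests that had not yet taken place, and that the result is bound to be spurious. The article does not support this. The sentence before the planned analysis speaks of the final diagnosis; etiology is collected again at three months and one year, after such tests can have occurred; and the baseline label itself may rest on a confirmatory test completed before the form was filled in. The article does not say which diagnosis is meant, so the odds ratios in step 4 are conditional.

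Size is also open to challenge. Tests meant to confirm a CMR finding could well come early, and the immortal-time bias is then modest. If sicker patients are tested more, the net direction is unknown.

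The sentence does not say that downstream use is fixed, ever/never, or in the same model as arm. A landmark, time-dependent or mediation analysis may stand in a fuller document that is not shown. Related plans also exist: reassessed etiology, HF therapies compared by strategy, and a cost regression.

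These points remove any claim of certainty. They do not remove the point itself. The article commits to an analysis with downstream use as the explanatory variable and refers it to a multivariable analysis, and the models it names for diagnosis and the CCE have no means of handling the timing of a variable that arises after randomisation. None of the related plans says how that variable is to be treated.

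**Conclusion.** The point holds in conditional form. If downstream use enters the named logistic models as a fixed covariate, its coefficient for the CCE can be biased by immortal time and confounding by indication, and HF admission may sit on both sides of the model. The illustrative one-year risk ratio for death, for a test with no effect, is about 0.42 to 0.48 with tests spread over year 1 and about 0.83 to 0.86 with tests within three months. With arm in the same model, some or all of the strategy effect that runs through testing can vanish. Reverse causation is a further problem only if the baseline diagnosis is the dependent variable.

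All these sizes rest on assumed rates, since the article gives none for testing or death. A reader might also infer that the primary result is at risk. It is not: the intention-to-treat chi-square comparison stands unless downstream use is put into its model, and the article does not say that it will be. The change is worth making because it is cheap and concerns the limitation the article itself raises.

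**What to change.** Replace the sentence in Limitations with a plan on these lines:

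- **(a)** Compare downstream testing (number of tests, and proportion of patients with biopsy, invasive hemodynamics or other tests) between randomised arms as an intention-to-treat outcome.
- **(b)** Describe its role in diagnosis using the one-year reassessed etiology by arm, and tabulate how many specific diagnoses in each arm rest on a downstream test. State the rule for patients who die or are lost before one year.
- **(c)** For any association between downstream use and clinical outcome, use a landmark (for example the three-month visit) or a time-varying covariate, exclude HF admissions from the predictor when the CCE is the outcome, and label the result exploratory and non-randomised.
- **(d)** Keep downstream use out of the model that gives the arm effect.

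The cost is wording and a little analysis. Reassessed etiology is already collected, and resource use is needed for the cost analysis anyway. The downside is that the association between testing and outcome can be reported only as exploratory.

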### Summary

In largely single center studies, CMR has been shown to offer a diagnostic advantage in specific HF disease states however its role in undifferentiated non-ischemic HF is largely unknown. Thus IMAGE-HF is a clinically relevant and timely study in an era of growing health costs and increasing pressure for fiscal responsibility. Given the available evidence and local experiences, we are confident that routine CMR will offer diagnostic and therapeutic advantages that ultimately improve patient outcomes at affordable costs.

## Trial status

Recruiting

## Appendix A

Standardization and quality assurance (IMAGE-QA)

The IMAGE-HF QA program standardizes several important aspects of clinical imaging:

1. defining best current imaging practice for standard-care tests

2. disseminating advanced imaging technology and standards

3. promoting structured reporting and comprehensive imaging QA

4. ensuring consistent interpretation and patient management recommendations

For the IMAGE-HF project 1-B (OUTSMART-HF), this includes standard operating procedures (SOPs) for echocardiography (ECHO) and cardiac magnetic resonance (CMR), as well as structured reporting elements and quality assurance review by QA-CORE labs (SOPs and CRFs are posted on the IMAGE-HF website).

Standard-care imaging protocols

*Echocardiography (ECHO)*:

IMAGE-HF 1-AB SOP ECHO-etiology (MHI)

Based on Montreal Heart Institute (MHI) CORE laboratory procedure manual for the IMAGE-HF 1-A study (AIMI-HF): TECHNICAL GUIDE FOR ECHOCARDIOGRAPHY October 2010 ([name], [name]). Detailed procedures are described for the required parasternal, apical and sub-costal view measurements, and instructions for transfer of DICOM format images to the MHI CORE lab.

Advanced imaging protocols

*Cardiac Magnetic Resonance (CMR)*:

IMAGE-HF 1-B/2-A SOP CMR-etiology-fibrosis (CanSCMR)

Based on Canadian Society for Cardiovascular Magnetic Resonance (CanSCMR) protocol recommendations v1.3 April 2009. Imaging parameters are included for assessment of LV function, inflammation, fibrosis and mitral valve regurgitation.

Common structured reporting elements

*ECHO*:

HF18C 1-B-etiology ECHO Report

The following parameters are included on the interpretation CRF: LV structure, LV systolic and diastolic function parameters, LV segmental wall-motion scores, RV structure and systolic function, severity of valve stenosis and regurgitation. Clinical interpretation as selected from a list of the most likely echocardiographic diagnoses, and confirmation that the diagnosis was communicated to the referring physician, are captured on the CRF.

*CMR*:

HF19C 1-B-etiology CMR Report

The following parameters are included on the interpretation CRF: LV and RV structure and systolic function parameters, LV myocardial edema and hyperemia, LV segmental wall-motion and tissue characterization scores, severity of valve regurgitation, and assessment of pericardial effusion. Clinical interpretation as selected from a list of the most likely CMR diagnoses, and confirmation that the diagnosis was communicated to the referring physician, are captured on the CRF.

Quality assurance CORE lab reviews (QA-CORE)

A subset of scans (10%) are targeted for over-reading interpretation at an experienced site identified as the CORE lab for each imaging modality. The first two scans (and 5% of the subsequent scans) from each imaging modality at each recruiting site are transferred to the corresponding modality QA-CORE lab for clinical interpretation and comparison to the site interpretation for quality assurance. Disagreements in the overall ECHO or CMR diagnosis are resolved by subsequent consensus review between the site and CORE lab, and recorded on the corresponding CRFs: *HF18-QA, HF19-QA.*

The QA-CORE lab for ECHO is established at the University of Ottawa Heart Institute, and the QA-CORE lab for CMR is at the University of Alberta.

## Abbreviations

CCE: Composite clinical endpoint; CMR: Cardiac magnetic resonance; CV: Cardiovascular; DSMB: Data and safety monitoring board; echo: Echocardiography; EF: Ejection fraction; HF: Heart failure; HFPEF: Heart failure with preserved ejection fraction; HFREF: Heart failure with reduced ejection fraction; ITT: Intent-to-treat; LA: Left atrial; LV: Left ventricular; MHFQ: Minnesota living with heart failure questionnaire; MMRM: Mixed methods repeated measures; NICM: Non-ischemic cardiomyopathy; NSTEMI: Non-ST-segment elevation myocardial infarction; QoL: Quality of life; STEMI: ST-segment elevation myocardial infarction.
